### Randomization

Doctors are randomly assigned to the intervention and control groups in a 1:1 ratio using Research Electronic Data Capture (REDCap) version 13.1.25 and a block size of 2/4. Stratification based on location is implemented to ensure an equal distribution of workload among the psychologists. Stratification will also allow for site comparison in the analysis. The intervention will last 3–4 months at each site, depending on the number of participating doctors.

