## Sample size calculation

Approximately 80 out of the around 90 eligible doctors (89%) are expected to participate in the study.

To achieve a power of 80%, a sample size of 2,080 patients (1,040 in each group) will be obtained by sampling 40 clusters (doctors) with 26 patient questionnaires in each group. In total we thus aim to collect 4160 questionnaires. The proportion in the intervention group is assumed to be 0.28 under the null hypothesis and 0.34 [33] under the alternative hypothesis assuming a difference between the group proportions of 0.06. Due to the lack of international consensus in this research area, an absolute change of 6% was agreed upon by mutual consensus in the steering group, as we believe such change would represent a clinical relevant difference for the patients. The proportion in the control group is assumed to be 0.28. The sample size calculation is based on a two-sided Z Test (unpooled) with intracluster correlation (ICC) set at 0.005, and significance level of the test at 0.05.

Each cluster size of 26 completed questionnaires per doctor at baseline and evaluations aligns with the recommendations from the CAT developers [32]. To meet the target we aim to distribute 30–40 questionnaires per doctor. Staff at each outpatient clinic will assist in the process.

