### Primary endpoint

The primary outcome measure is the change in percentage of “excellent” scores measured by the CAT questionnaire on each of the 14 items. All items are answered on a numerical scale from 1 (poor) to 5 (excellent), as well as the option "not relevant". The difference in percentage of "excellent" scores between patients treated by doctors in the intervention and control groups will be analyzed by binary regression using robust variance estimation and taking clustering of patients seeing the same doctor into account. The model will include participating site as a covariate. Due to the randomization and the high number of observations, exchangeability is expected between the patients in the two study groups, and hence, no further covariates are planned in the model. Exchangability will be investigated using standardized differences. A standardized differences > 0.1 indicate imbalance between groups. Effects will be reported on relative and absolute scales as relative risk (RR) and risk differences (RD).

Data will be collected from the patients’ questionnaires on sociodemographic information, years with cancer, disease stage (curable, incurable, unknown), relation to the doctor (first meet or not), and participation or not of relatives at the consultation. Subgroup analysis stratified by site will be performed.

All analyses will be evaluated as intention to treat. The proportion of missing data in the patient questionnaires will be investigated. If the proportion is less than 5%, a complete case analysis will be performed. If missing data exceeds 5%, an imputation analysis will be applied [47].

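### The questionnaire count is no reason to expect balanced patient mix when only about 40 doctors per arm are randomised; prespecify a case-mix covariate instead

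*Protocol article*

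**What the plan says.** The Randomization section makes the doctor the unit of allocation: "Doctors are randomly assigned to the intervention and control groups in a 1:1 ratio". The only stratification factor is site: "Stratification based on location is implemented to ensure an equal distribution of workload among the psychologists". The Sample size calculation section gives the number of units, "Approximately 80 out of the around 90 eligible doctors (89%) are expected to participate in the study", and the layout, "sampling 40 clusters (doctors) with 26 patient questionnaires in each group". Patients enter by attending a doctor's outpatient clinic (Participants, Patients).

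The Primary endpoint section plans a binary regression with robust standard errors that allow for patients sharing a doctor, and with site as covariate. It justifies stopping there: "Due to the randomization and the high number of observations, exchangeability is expected between the patients in the two study groups". Standardised differences are to be examined, with 0.1 as the mark of imbalance. Patient factors that could describe case mix are collected but not in the model, among them "disease stage (curable, incurable, unknown), relation to the doctor (first meet or not".

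**The concern.** The stated reason belongs to a trial that randomises patients. With doctors as the unit, a covariate that runs along a doctor's patient list is balanced only as well as 40 lists per arm allow, however many forms each list yields. The same section recognises clustering when it sets the variance and overlooks it when it argues about balance.

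This matters because the rationale decides the covariate set of the primary model. If patient mix differs between arms and is related to excellent ratings, the estimate in this trial is displaced. Any adjustment decided after the imbalance is seen would be data-driven.

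**Working it through.** **1. The plan's own figure.** Inputs from Sample size calculation: "To achieve a power of 80%, a sample size of 2,080 patients (1,040 in each group) will be obtained"; "The proportion in the intervention group is assumed to be 0.28 under the null hypothesis and 0.34"; control 0.28; two-sided unpooled Z test at 0.05; outcome ICC 0.005; 26 forms per doctor.

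- Independent patients: n = (1.960 + 0.842)² × (0.28×0.72 + 0.34×0.66) / 0.06² = 928.8 per arm.
- Design effect: 1 + 25 × 0.005 = 1.125, giving 928.8 × 1.125 = 1,044.9 per arm against the stated 1,040.
- Power at 40 × 26 per arm: SE = √(0.4260/1040 × 1.125) = 0.02147; 0.06/0.02147 − 1.96 = 0.835; power 79.8%.

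The sample size reproduces.

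**2. Chance of passing the 0.1 limit.** The standardised difference of one covariate with ICC ρ has SD = √[(2/1040) × (1 + 25ρ)]. The article gives no ρ; the range is assumed. Case mix is taken at one period. Stratification by site is ignored; it would remove any between-site part.

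| ρ | Effective n per arm | SD | P(beyond ±0.1) | 95% range, 50% prevalence (points) |
|---|---|---|---|---|
| 0 | 1,040 | 0.044 | 2.3% | ±4.3 |
| 0.05 | 462 | 0.066 | 12.8% | ±6.4 |
| 0.10 | 297 | 0.082 | 22.3% | ±8.0 |
| 0.20 | 173 | 0.107 | 35.2% | ±10.5 |
| 0.30 | 122 | 0.128 | 43.4% | ±12.5 |

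**3. Shift in the treatment estimate.** For a factor with 50% prevalence that changes the excellent rate by β (assumed), the 95% range of the shift is 1.96 × SD × 0.5 × β. The factor alone adds β² × 0.25 × ρ / (0.31 × 0.69) to the outcome ICC.

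| ρ | Shift, β = 10 points | Outcome ICC added | Shift, β = 20 points | Outcome ICC added |
|---|---|---|---|---|
| 0.05 | ±0.64 | 0.0006 | ±1.29 | 0.0023 |
| 0.10 | ±0.80 | 0.0012 | ±1.61 | 0.0047 |
| 0.20 | ±1.05 | 0.0023 | ±2.11 | 0.0094 |
| 0.30 | ±1.25 | 0.0035 | ±2.51 | 0.0140 |

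The two cells above 2 points need more between-doctor variation than the planned total of 0.005.

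**4. Limit implied by the planned ICC.** All doctor-level variation together gives a between-arm SD of √(0.005 × 0.31 × 0.69 × 2/40) = 0.0073, or ±1.4 points (95%). At an outcome ICC of 0.02 (assumed) this doubles to about ±2.9. The ±1.61 in step 3 is slightly larger than ±1.4 because it also contains patient-level sampling variation.

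**5. Simulation.** 80 doctors × 26 patients, no treatment effect, 50% prevalence, linear probability model with doctor-clustered standard errors, site omitted, 1,500 runs per scenario, ρ = 0.1 or 0.3, β = 10 or 20 points.

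- Over all runs the mean error without adjustment was at most 0.05 points, and type I error was 5.5% to 6.0% (5.5% to 6.8% with adjustment).
- In runs with imbalance above 0.1, the unadjusted estimate was shifted by 0.8 to 1.7 points on average; the 1.7 comes from ρ = 0.3 with β = 20, which exceeds the planned ICC. Adjustment reduced the shift to 0.1 points or less.
- The SD of the estimate fell with adjustment in every scenario, from 0.0200 to 0.0195 at the least and from 0.0229 to 0.0193 at the most.

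**The case against.** Chance imbalance between randomised doctors is random error, and the planned variance carries it; step 5 confirms this. A model adjusted only for the stratification factor is legitimate, so the gain from further covariates is efficiency. This stands, and it limits the point.

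The endpoint is a change and baseline forms exist for the same doctors. Stable features of a doctor's list would then partly cancel, while steps 2 to 5 treat a single period. This stands in part: site is the only covariate that the article names, and it does not spell out how baseline enters the model.

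Disease stage is reported by patients, and at evaluation the patients are new and see doctors who may have been trained. What a patient answers could depend on how well the doctor explained the situation, so requiring it in the primary model risks adjusting for an effect of the intervention. This stands and shapes the fix.

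The article refers to predefined analysis plans that are not shown, and these may say what follows when the 0.1 limit is passed. That silence is therefore not counted here. The objection does not rescue the rationale itself, because the article states both the reason and the covariate set.

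Finally, the article does not say that doctors' lists differ in stage or first meetings; it describes only varied roles and amounts of patient contact. Clustering of case mix is plausible but assumed.

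**Conclusion.** The reason given for leaving case mix out is wrong for a doctor-randomised trial. The number of questionnaires does not deliver patient-level balance; 40 doctors per arm is what counts. At assumed covariate ICCs of 0.05 to 0.30, the plan's own imbalance limit would be exceeded 13% to 43% of the time per covariate, instead of 2%.

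The consequence is moderate: some lost precision, in a design whose recomputed power is 79.8%, and a possible displacement of the one estimate obtained. Doctor-level variation is bounded at about ±1.4 points under the planned outcome ICC, and more if that ICC proves higher.

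A reader might infer that the primary comparison is biased or its test invalid. The documents do not support that: allocation is random and the variance is clustered by doctor. A reader might also infer shifts of 2 points or more; those need assumptions that contradict the planned ICC of 0.005. Prevalence, prognostic effect and covariate ICC are all assumed here, because the article gives none of them.

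**What to change.** Delete the sentence that rests exchangeability on randomisation and the number of observations. Replacement wording:

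*Because doctors rather than patients are randomised, the primary model includes site and relation to the doctor (first meeting or not). RD and RR are obtained by marginal standardisation, with standard errors clustered by doctor. Sensitivity analyses are the model with site only and the model that adds disease stage. Standardised differences are descriptive and do not change the model.*

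First meeting or not is suited to the primary model because training is unlikely to alter it. Disease stage belongs in the sensitivity model because it is patient-reported after doctors are trained. Fixing this now also removes any need to choose covariates after an imbalance has been seen.

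Cost: no new data, since both items are already on the questionnaire; slightly more analysis work; and forms with a missing covariate need the imputation that the plan already foresees.

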## Statistical analysis plan

All statistical analyses will be performed in close collaboration with a statistical consultant based on predefined statistical analysis plans. A 95% confidence interval is applied. P values < 0.05 are considered statistically significant. STATA version 18 will be used for all analyses, and all steps of data management, coding and analysis will be logged.

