### Secondary endpoints

*Self-efficacy in health communication*: Change in the mean sumscore of the SE-12 Survey. All items are answered on a numeric scale at 1–10 as well as the option “not relevant”.

*Burnout*: Change in total score for CBI part 2 (seven questions) and part 3 (six questions). All items are answered on a numeric scale from 0 to 4.

*Jobsatisfaction*: Change in the mean sum score of the MTU. All items are answered on a numeric scale 1–7.

Hypotheses will be tested using paired t test in case of normality and Wilcoxon signed rank test in case of non-normality comparing the intervention and control groups.

Data will be collected on the doctors’ age, sex, spoken language at home, years since university degree, job title and prior participation in communication training. Explorative subgroup analysis will be performed stratified by site and doctors’ experience (years since university degree).

A doctor participating in two or more intervention days with a psychologist is considered compliant with the intervention. Doctors’ questionnaires will be evaluated as intention to treat. In case of crossover, per-protocol analysis will be performed as sensitivity analysis. The proportion of missing data in the doctors' questionnaires will be investigated. If the proportion is less than the expected 5%, a complete case analysis will be performed. In case of missing data above 5%, appropriate imputation methods will be applied.

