## Discussion

### Strengths

A randomized, controlled trial design enhances the internal validity of the study by randomly assigning oncologists to the intervention or control group. This will reduce selection bias and allow for a more robust assessment of the impact of On-site SCT. Additionally, conducting the study at three sites increases the diversity and representativeness of the sample in providing a stronger basis for generalization and demonstrating the intervention's effectiveness across settings.

The on-site approach allows doctors to balance clinical duties (seeing patients) with ongoing, individualized learning. If effective, On-site SCT should be considered a part of a continuing education program. Thus, it should be seen as a viable alternative to an external three-day full-day course in communication skills, where the costs would include not only the doctor's complete absence from clinical duties but also the course fee. Additionally, fostering collaboration between psychologists and oncologists promotes an interdisciplinary approach to patient care.

The primary endpoint of the study, change in percentage of "excellent" scores, is assessed using a validated questionnaire with expected data from more than 4,000 patients. The patient-centered approach adds value to the study by capturing the patients’ perception of effective communication. The study collects both quantitative and qualitative data from the participating doctors to comprehensively evaluate the effect of the intervention.

As described, selection bias may occur, as the doctors who would potentially benefit the most from the intervention might be more likely to decline participation. To address this hypothesis, we aim to collect baseline CAT questionnaires from patients of all eligible doctors enabling comparison of those participating and not participating. As described, the analysis necessitates a minimum of five individuals in the last group. Conducting tthe analysis allows for a better understanding of any differences between the two groups and helps mitigate the potential impact of selection bias.

It is a strength that the intervention has been tested and thoroughly described in a manual (15 pages). It is developed in Danish but can be translated into other languages to enable international dissemination of the concept.

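### A comparison of sites is intended, but the only subgroup method named for the primary endpoint is analysis within each site, and no arm-by-site interaction is described

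*Protocol article*

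**What the plan says.** Under Randomization, the article gives a second reason for stratifying by location: "Stratification will also allow for site comparison in the analysis".

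Under Primary endpoint, the main analysis is a binary regression with robust variance that allows for clustering by doctor. On site it says: "The model will include participating site as a covariate". It adds that "no further covariates are planned in the model", on the ground that randomization and the large number of observations should make the patient groups exchangeable. Effects are to be reported as relative risks (RR) and risk differences (RD). The subgroup plan is one sentence: "Subgroup analysis stratified by site will be performed".

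The opening of the Statistical analysis plan section sets 95% confidence intervals and P < 0.05 for all analyses, with no separate rule for subgroups. It also says that the analyses will be "based on predefined statistical analysis plans"; those plans are not shown.

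**The concern.** The stated purpose and the named method do not match. Whether the training works differently in the three departments is a question about the difference between site-specific effects. Repeating the arm comparison inside each site does not estimate or test that difference. A model with site as a main effect only does not do so either, because it assumes a common effect.

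The practical risk lies in interpretation. Three underpowered within-site results, read against the article's only threshold of P < 0.05, will often disagree by chance. A report could then suggest that the training works in one department and not in another when the data do not show it.

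**Working it through.** **Inputs.** From Sample size calculation: proportions 0.28 and 0.34, 40 doctors per arm, 26 questionnaires per doctor, ICC 0.005, two-sided unpooled Z test at 0.05, power 80%. From Setting: three sites. Doctors per site are not given, so the split is an assumption. As in the plan's own calculation, each questionnaire contributes one proportion and the arms are compared at one time point.

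**Reproducing the plan's figure.**
- Design effect: 1 + (26 − 1) × 0.005 = 1.125.
- Variance term: 0.28 × 0.72 + 0.34 × 0.66 = 0.2016 + 0.2244 = 0.4260.
- n per group: 1.125 × 0.4260 × (1.960 + 0.842)² / 0.06² = 1.125 × 928.8 = 1,044.9, against 1,040 stated.
- SE at 1,040 per group: √(0.4260 × 1.125 / 1,040) = 0.0215. Power: Φ(0.06/0.0215 − 1.96) = 79.8%. The plan's calculation is reproduced.

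**The same formula within one site (even split assumed).**
- Doctors per arm per site: 40/3 = 13.33. Questionnaires per arm per site: 13.33 × 26 = 346.7.
- SE: √(0.4260 × 1.125 / 346.7) = 0.0372.
- Power: Φ(0.06/0.0372 − 1.96) = 36.5%.

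**Pattern across three sites when the true effect is 6 points at each.**
- All three significant: 0.365³ = 4.8%.
- None significant: 0.635³ = 25.7%.
- Mixed (one or two of the three): 100 − 4.8 − 25.7 = 69.5%.

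**Sensitivity of the mixed pattern.**

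| Assumption varied | P(mixed) |
|---|---|
| Doctors per arm by site 16/14/10, 10/15/15, 20/10/10, 24/8/8 (ICC 0.005) | 70% to 72% |
| t reference with doctors as units (even split, ICC 0.005) | 67% |
| ICC 0.02 (even split) | 61% |
| ICC 0.05 (even split) | 49% |
| ICC 0.10 (even split) | 38% |

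The split hardly matters; the ICC does. As the ICC rises, within-site power falls and the outcome with no significant site becomes more common (50% at ICC 0.05, 62% at 0.10).

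**Simulation check.** In 20,000 beta-binomial trials with a 13/13/14 split, ICC 0.005 and a common 6-point effect, the pattern was mixed in 71%, and in 82% of the trials with a significant overall result. A 2-df test of arm-by-site heterogeneity rejected in 6%, close to its nominal 5%. At ICC 0.05 the corresponding figures were 51% mixed, 79% mixed among trials significant overall, and 6% rejection.

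**What an interaction test could detect.** The SE of the difference between two sites' effects is 0.0372 × √2 = 0.0526. For 80% power, the true difference must be about (1.96 + 0.84) × 0.0526 = 0.147, or about 15 points.

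**The case against.** The strongest objection is that the article is silent here rather than wrong. It refers to predefined analysis plans, and whether a subgroup analysis carries an interaction term is often settled there. This stands in part: the unseen plan may contain the interaction, so it cannot be said to be absent from the trial's plans. But the article states a comparative purpose and names a method that does not serve it, and that mismatch is in the text.

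A reader might infer that the trial will judge site effects by which sites reach P < 0.05. No sentence says so. The article also applies 95% confidence intervals and reports RR and RD, so site-specific estimates with intervals fit its wording. The 70% figure describes what follows if readers count significant sites; it does not describe a rule the article adopts. Nor does the statement that "no further covariates are planned in the model" exclude an interaction, since it concerns adjustment for imbalance between patients.

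A reader might extend the point to doctors' experience, because Secondary endpoints says "Explorative subgroup analysis will be performed stratified by site and doctors’ experience (years since university degree"). That analysis is labelled explorative and concerns doctor-reported outcomes only. The article gives neither experience groups nor effect sizes, so the figures above do not carry over.

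A reader might also take the phrase "effectiveness across settings" under Strengths as a promise of site-by-site conclusions. It describes the benefit of a multicentre design and does not rest on the subgroup analysis.

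Finally, it is fair to say that the interaction test will seldom settle the question: about 15 points is 2.5 times the assumed 6-point effect. Its value is in guarding against reading noise as a site difference.

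**Conclusion.** The point holds as a minor one, for the site analysis of the primary endpoint only. The article intends to compare sites but describes only within-site analyses. On its design inputs and an assumed even split, a common 6-point effect would produce a mixed pattern of site-level significance in about 70% of trials, whereas a heterogeneity test would wrongly signal a site difference in about 6%. The 70% depends on the planned ICC of 0.005 and drops to about 49% at 0.05 and 38% at 0.10; it changes little with the split of doctors over sites. The pooled primary analysis and its conclusion are unaffected.

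**What to change.** In Primary endpoint, replace the subgroup sentence with a statement that:
- differences between sites in the effect of training are assessed by an arm-by-site interaction (joint 2-df test) in a single model, with the same allowance for clustering by doctor;
- site-specific RDs and RRs with 95% confidence intervals are descriptive only, and no conclusion rests on which sites reach P < 0.05;
- the interaction test has low power, needing a difference of about 15 points between two sites for 80% power under the design assumptions and an even split, so a non-significant result does not show that the effects are equal.

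If the full analysis plan already says this, a cross-reference is enough. The cost is a few lines of text and one additional model; no new data are needed and the sample size does not change.
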